## 3. Methods

### 3.1. Trial Design

This study was structured as an acute, randomized crossover clinical trial to evaluate two meals with identical protein content but differing in fat and carbohydrate proportions (HP-HF-LC and HP-LF-HC). Each participant consumed both meals on separate days, with a minimum one-week washout period between sessions to eliminate carryover effects. The stages of intervention and evaluation were outlined in Figure 1. 

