### 3.3. Sample Size

Due to the novelty of our study and the absence of prior similar research, the sample size was determined based on the study by Soares et al. (12). The respiratory exchange ratio was selected as the main variable, with the alpha error set at 0.05 and the beta error at 0.2. The sample size was calculated using the two-mean test formula for a quantitative trait in two independent groups. To account for potential attrition, the final sample size was determined to be 30 participants.

$$n=\frac{{\left(Z_{1-\frac{\alpha }{2}}+Z_{1-\beta }\right)}^{2}\left(\sigma_{1}^{2}+\sigma_{2}^{2}\right)}{{\left(\mu_{1}-\mu_{2}\right)}^{2}}$$

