### 4.1. Assignment of Interventions: Allocation Sequence Generation

This randomization was conducted using a simple randomization technique to allocate participants in a 1:1 ratio to one of two sequence groups: Sequence 1, where participants received meal A in the first week and meal B in the second week; and sequence 2, where participants received meal B in the first week and meal A in the second week. Fifteen participants were allocated to each sequence group. 

The random number table was used to generate the allocation sequence. To ensure allocation concealment, an independent individual not affiliated with the study placed the random sequence into opaque, sealed envelopes. At baseline, each participant randomly selected one envelope, and the sequence inside determined the order in which they received the meals. Additionally, participants were blinded to the order of meal administration. Meals were prepared in advance to appear as identical as possible, with minimal distinguishing features, so that participants did not know which diet they were receiving at any stage. Standardization emphasized uniform meal presentation with minimal features to maintain participant blinding to the meal order. 

This study was a randomized controlled trial employing a crossover design and involving a total of 30 participants (15 women and 15 men). During the first phase, each participant received one of the two meal interventions: Either an HP-HF-LC meal or an HP-LF-HC meal. In the second phase, participants received the alternate meal. Due to the crossover design and the differences in food components between phases, blinding was feasible only for the sequence groups. 

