### 4.7. Data Management and Analysis

Data from anthropometric measurements, blood sampling, and calorimetry were recorded by the lead researchers using Microsoft Excel. Each participant's data was coded to ensure confidentiality, with only the principal researchers having access to identifying information. The coding system consisted of a three-digit number followed by letters A to E. The first digit (1 or 2) indicated the type of intervention, the next two digits denoted the participant number, and the letters represented the fasting stage and subsequent hours post-intervention. 

Data were reported as means ± standard deviations for continuous variables that followed a normal distribution, while non-normally distributed continuous variables were presented as medians along with interquartile ranges. Categorical variables were summarized using frequency distributions expressed as percentages. To compare conditions, independent two-sample *t*-tests were employed. Statistical analyses were conducted using generalized linear models (GLM) within SPSS version 22. The carryover effect was assessed, and if found significant, the influence of time and type of meal was analyzed. In the absence of a significant carryover effect, comparisons were made in parallel during the first period using covariance analysis. A two-factor repeated measures design was evaluated using generalized linear mixed models to examine the impact of time and type of meal across various phases of the study.

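### The carryover decision rule is reversed: it limits the meal comparison to the first period when no carryover is found, which is the case the washout is meant to secure

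*Protocol article*

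**What the plan says.** The trial is a two-period crossover. Section 3.1 (Trial Design) has every participant eat both meals, "with a minimum one-week washout period between sessions to eliminate carryover effects". Section 4.1 fixes the sequence groups: "Fifteen participants were allocated to each sequence group".

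Section 4.7 (Data Management and Analysis) then gives a conditional rule in two adjacent sentences:

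- Carryover significant: "The carryover effect was assessed, and if found significant, the influence of time and type of meal was analyzed".
- Carryover not significant: "In the absence of a significant carryover effect, comparisons were made in parallel during the first period using covariance analysis".

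The section closes with a model to which no condition is attached: "A two-factor repeated measures design was evaluated using generalized linear mixed models to examine the impact of time and type of meal". It does not say which of these analyses is primary.

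**The concern.** The conventional two-stage rule for a crossover compares meals within person over both periods when carryover is not detected, and retreats to the first period when it is. The first period precedes any second meal, so it is the one part of the data that carryover cannot reach. Section 4.7 states the opposite pairing. Nothing justifies dropping the second period when no carryover has been found, and when carryover has been found the text no longer confines itself to the uncontaminated period.

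At stake is the reason for running a crossover at all. Followed literally, in its expected case the plan makes the meal comparison between two groups of 15 instead of within 30 people.

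**Working it through.** **Inputs from the protocol article.** 30 participants, 15 per sequence (sections 3.3 and 4.1); two-sided alpha 0.05 and power 0.80 (section 3.3); washout of at least one week (section 3.1).

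**Assumptions, since the article gives no values.** Within-person correlation between periods, rho, of 0.5, 0.7 or 0.8; correlation r between baseline and outcome of 0.5 to 0.9; equal SDs; carryover tested at 5%.

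**The plan's own figure.** The 30 cannot be reproduced, because section 3.3 states no means, SDs or attrition rate. Solving its formula backwards gives a difference of (1.960 + 0.842) × √(2/30) = 0.723 SD if 30 is the number per group, or 2.802 × √(2/15) = 1.023 SD if 15 is. The point below does not depend on this figure.

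**Step 1: how often each branch is taken.** With no true carryover, a 5% test is non-significant 95% of the time (90% for a 10% test). That is the first-period branch.

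**Step 2: precision in each branch.**

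- Both periods: variance of the meal difference = 2 SD² (1 − rho)/30, 28 df.
- First period, unadjusted: 2 SD²/15, 28 df.
- First period, covariance analysis: 2 SD² (1 − r²)/15, 27 df.

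The unadjusted variance ratio is (2/15) ÷ (2(1 − rho)/30) = 2/(1 − rho), or 4.0, 6.7 and 10 at rho 0.5, 0.7 and 0.8. With covariate adjustment it is 2(1 − r²)/(1 − rho). Where r equals rho this gives 3.0, 3.4 and 3.6.

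**Step 3: power (noncentral t).** For each rho, take the difference at which the both-period analysis has 80% power and apply it to the first period alone.

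| rho | Difference (SD) | First period, unadjusted | ANCOVA, r = 0.5 | ANCOVA, r = 0.7 | ANCOVA, r = 0.9 |
|---|---|---|---|---|---|
| 0.5 | 0.53 | 29% | 37% | 50% | 89% |
| 0.7 | 0.41 | 19% | 24% | 33% | 70% |
| 0.8 | 0.34 | 14% | 18% | 24% | 53% |

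In one corner (rho 0.5, r 0.9) first-period ANCOVA exceeds 80%. The both-period comparator here uses no baseline, so that cell sets an adjusted analysis against an unadjusted one.

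**Step 4: the rule as a whole, simulated** (15 per sequence, unadjusted tests, 60,000 runs per cell; rho 0.5 / 0.7 / 0.8).

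- Power of the written rule where the full crossover has 80%: 30% / 21% / 16%.
- Type I error of the written rule, with no meal effect and no carryover: 2.7% / 2.2% / 1.7%.
- Type I error with the branches swapped: 7.3% / 7.9% / 8.1%.

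**The case against.** **The closing mixed model uses both periods anyway.** This partly stands. That sentence carries no condition, so a reader who infers that the second period is simply thrown away goes further than the text. But the model is not named primary and does not cancel the rule above it. What remains is a reversed rule next to a model whose relation to it is undefined.

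**The significant branch never says both periods.** True. It says only that meal type and time are analysed. Both periods is the natural reading, because only the other branch is confined to the first. The main harm lies in that other branch, where the restriction is explicit.

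**The plan specifies covariance analysis, so unadjusted power overstates the loss.** This stands, which is why the adjusted range leads. The loss depends heavily on a baseline correlation that the article does not give.

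**A stronger reading: under real carryover the plan would report a biased result.** A reader might infer this, but it is mostly untrue. With an assumed carryover of 0.8 SD and no meal effect, the pre-test is significant in only 23%, 21% and 20% of trials (rho 0.5, 0.7, 0.8). In the rest, the written rule reports the first-period comparison, which carryover cannot bias. Its rejection rate there is 15%, 19% and 21%, against 56%, 78% and 92% for an analysis that always uses both periods. That scenario is therefore no argument for the change. The case for it rests on the washout making carryover implausible.

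**It may be a wording slip.** Possibly. The text would still need correcting, since an analysis that quietly departed from it would depart from the published plan.

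**Conclusion.** Wrong as written. The two branches in section 4.7 are exchanged, and no other section corrects them. In the expected case of no carryover, about 95% of trials would go to a 15 versus 15 first-period comparison. Where the full crossover has 80% power, that comparison has about 37–89%, 24–70% and 18–53% by covariance analysis at rho 0.5, 0.7 and 0.8, and about 29%, 19% and 14% without adjustment. These figures rest on assumed correlations; the reversal itself rests on the text alone.

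A reader might also infer an inflated false-positive rate. The calculations do not support that: with neither a meal effect nor carryover, the written rule rejects about 2–3% of the time, below the nominal 5%.

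**What to change.** Delete the two conditional sentences in section 4.7. Make the mixed model already named there the single primary analysis, whatever the carryover test shows:

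- data from both periods;
- fixed effects for sequence, period, meal, time and meal-by-time;
- random effects for participant and participant-by-period;
- the fasting value of each period as baseline.

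Justify this by the washout of at least one week, report the sequence or carryover effect descriptively, and show the first-period covariance analysis only as a sensitivity analysis. Do not merely swap the branches, because the pre-test would then inflate type I error, as shown above.

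The cost is a rewording in section 4.7, and in the statistical analysis plan if it carries the same rule; no new data are needed. The downside is that the both-period estimate would be biased by half the carryover difference if carryover were real. The washout makes that unlikely, and the sensitivity analysis offers a check, though a weak one at 15 per group.

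### The crossover mixed model is described with time and meal only; period and sequence should be added, and the simple-randomisation label reconciled with the exact 15:15 split

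*Protocol article*

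**What the plan says.** Section 4.7 of the protocol article gives the model for the crossover data: "A two-factor repeated measures design was evaluated using generalized linear mixed models to examine the impact of time and type of meal". The sentence ends by referring to various phases of the study, but lists no phase, period or sequence factor and no covariate.

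Two other statements in section 4.7 bear on this. One is a carryover step: "The carryover effect was assessed, and if found significant, the influence of time and type of meal was analyzed". The other is a first-period analysis in which "comparisons were made in parallel during the first period using covariance analysis"; its covariate is not named. The data code in the same section has a first digit for the meal, two digits for the participant, and a letter from A to E, where "the letters represented the fasting stage and subsequent hours post-intervention". The fasting measurement is thus the first of the coded time points.

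On allocation, section 4.1 says: "This randomization was conducted using a simple randomization technique to allocate participants in a 1:1 ratio to one of two sequence groups". It then reports: "Fifteen participants were allocated to each sequence group". The sequence came from a random number table and was placed in sealed envelopes, of which each participant drew one. The mix of envelopes is not given. The same section gives 15 women and 15 men, and section 4.9 plans analyses by sex. Section 4.10 replaces participants who cannot be rescheduled, without saying which sequence the replacement takes.

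**The concern.** In a two-period crossover each participant's meal difference contains the meal effect plus or minus the period effect, with the sign set by sequence. A first visit can differ from a second for reasons unrelated to the meal, such as familiarity with the calorimetry mask. Without a period term, that difference has two places to go. With equal sequences it inflates the residual variance and costs power. With unequal sequences part of it also enters the meal estimate.

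Whether the sequences are equal by design therefore matters, and section 4.1 leaves this unclear: the named method does not guarantee the reported split. Even if the overall split is exact, nothing described makes it hold within each sex or after a replacement.

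The fasting value raises a related question. If it is a level of time and the meal main effect is read from the model, a measurement that precedes the meal is averaged into the effect of the meal.

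**Working it through.** **Inputs.** From the protocol article: N = 30, 15 per sequence, 15 women and 15 men (section 4.1); calorimetry at five time points, one of them fasting (section 4.5.1); blood sampling and satiety at three, one of them fasting (sections 4.5.3 and 4.11.1). Assumed, because the article gives no figure: a period effect π of 0.5 or 1.0 SD of the within-person meal difference, and a true meal difference of 0.55 SD of that difference. The meal comparison is treated as one paired difference per participant.

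**1. The stated split under simple randomisation.**
- P(exactly 15:15) = C(30,15)/2^30 = 155,117,520/1,073,741,824 = 0.144.
- P(18:12 or more unequal) = 2 × P(Bin(30, 0.5) ≤ 12) = 0.362.

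An exact 15:15 is possible under simple randomisation, but it is what a fixed set of 15 + 15 envelopes would produce every time.

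**2. Bias without a period term.** The difference A − B has mean δ − π in the sequence that takes A first and δ + π in the other. The unadjusted mean difference is therefore off by π × (n1 − n2)/n in absolute size.

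| Split | Share of π passed on |
|---|---|
| 15:15 | 0 |
| 16:14 | 2/30 = 6.7% |
| 18:12 | 6/30 = 20% |
| 20:10 | 10/30 = 33% |

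At the stated split the overall bias is zero. One withdrawal replaced in the opposite sequence would make it 16:14.

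**3. Precision at 15:15.** Without the term, the variance of the paired difference rises from 1 to about 1 + π². At π = 0.5 SD, √(1 + 0.25) = 1.118, so intervals are about 12% wider. Simulation (40,000 runs, N = 30) gave:

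| Period effect | Power without period term | Power with period term |
|---|---|---|
| 0 | 0.83 | 0.83 |
| 0.5 SD | 0.76 | 0.83 |
| 1.0 SD | 0.55 | 0.83 |

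Type I error without the term fell to 0.028 and 0.005 at 0.5 and 1.0 SD; with it, the rate stayed at about 0.05. At 15:15 the unadjusted test is conservative, not misleading.

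**4. Sex subgroups.** Fifteen is odd, so 8:7 is the best split within a sex, and it passes on 1/15 = 6.7% of π. With 15:15 overall and sequence unrelated to sex, the number of women in one sequence is hypergeometric (30, 15, 15). P(10:5 or more unequal) = 0.143, and 10:5 passes on 5/15 = 33%. The other sex is then unequal in the opposite direction, so the male–female contrast in the meal effect carries twice the share: 2 × 6.7% = 13% at best and 2 × 33% = 67% at 10:5.

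**5. Fasting as a time level.** If the meal main effect is an equal average over all time points, the fasting point contributes no meal effect. The average is then 4/5 of the post-meal effect for calorimetry and 2/3 for the three-point outcomes. This applies only if the main effect is the quantity reported; a meal × time term would avoid it, but none is named.

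**The case against.** The strongest reply is that the wording is condensed. A two-factor description may name the within-person factors without listing every term, section 4.1 uses phase for the two periods, and a full list could sit in an analysis plan that is not shown. That is fair as a limit on certainty. Even so, the article does describe the model, calls it two-factor and names the two factors, and neither is period.

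Several stronger readings are tempting, and the document does not support them:

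- *The overall meal effect is biased.* Not at the stated 15:15, where the period effect cancels. Even averaged over all splits that simple randomisation could give, simulated type I error stayed near 0.05 without the term. Bias arises only given an actual imbalance and a non-zero period effect, and no period effect is documented.
- *Period cannot be modelled because the code omits visit order.* The code is a confidentiality label. Sequence is fixed by the envelope, and sequence with meal gives period. The planned carryover and first-period analyses need visit order anyway.
- *The code reveals the meal to the laboratory.* Nothing says that tubes carry this code or that the operator knows its key.
- *The fasting value is ignored.* It is a coded time point and may also be the unnamed covariate in the first-period analysis. Only its role in the mixed model is unclear. Any figure for the variance that baseline adjustment saves would rest on assumed correlations (25–49% for correlations of 0.5–0.7).
- *Sequence is wholly absent.* A carryover assessment implies a sequence contrast somewhere; it is absent only from the mixed model as described.
- *Allocation should have been in blocks stratified by sex.* That is a preference, and it cannot be applied to an allocation already made.

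**Conclusion.** The point holds in limited form. The mixed model as described lacks period and sequence. At 15:15 the consequence is lost precision: about 12% wider intervals, and power of 0.76 instead of 0.83, if the period effect is 0.5 SD of the paired difference. Both figures rest on that assumption and on the assumed meal difference of 0.55 SD; with no period effect there is no loss. Bias is confined to situations where balance fails: 6.7% of the period effect after one replacement in the opposite sequence, at least 6.7% within each sex, and 33% at a 10:5 split within a sex.

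Separately, the simple-randomisation label and the exact 15:15 in section 4.1 do not sit comfortably together (probability 14%). This is a reporting conflict to be reconciled and does not show that the allocation was faulty.

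**What to change.** In section 4.7, specify meal, time, meal × time, period and sequence as fixed effects, with participant and visit within participant as random effects. Enter the same-visit fasting value as a baseline covariate, with time restricted to the post-meal points, so that it is not averaged into the meal main effect. Use the same terms in the analyses by sex.

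In section 4.1, describe the allocation as it was carried out. If 15 envelopes of each sequence were drawn without replacement, say so and delete the word simple; if allocation was truly simple, say that 15:15 arose by chance. In section 4.10, state which sequence a replacement takes.

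The cost is wording and a few degrees of freedom. In the simulation at 15:15 with no period effect, adding the period term left power at 0.83. No new data are needed.

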**Figure 1. A157244FIG1:**
[figure not shown]
Stages of intervention and evaluation

Two days prior to the intervention, participants were contacted and instructed to abstain from alcohol consumption, strenuous physical activity, and any dietary changes until their scheduled visit. On the day of the intervention, participants were required to arrive at the Imam Reza Hospital Research Center at 7:00 a.m., using personal vehicles or public transportation while minimizing physical exertion. Participants observed a 12-hour fasting period prior to their arrival, during which they could consume only water and had to refrain from smoking. 

Upon arrival, eligibility for participation was reconfirmed, followed by the measurement of anthropometric parameters. Participants completed an appetite questionnaire and underwent an indirect calorimetry (IC) assessment in a fasting state. Immediately after the IC assessment, a venous blood sample was collected. Participants then consumed the assigned intervention meal within 10 minutes under researcher supervision. 

During the postprandial phase, IC and appetite response assessments were conducted four times at one-hour intervals. Blood samples were collected twice: One hour after the meal and again during the final hour of the assessment. All tests were performed under standardized conditions and administered by the same personnel to ensure consistency. Figure 2 provided a schedule of the intervention and assessments, with time intervals selected based on prior studies. 

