## 4. Results

The CONSORT diagram was presented in Figure 3. As this article was a protocol study, it was anticipated that the diagram would be completed upon the study's conclusion. The primary outcome of this crossover trial was to investigate and compare the postprandial acute effects of two different meals on basal metabolic rate and satiety in overweight and obese men and women. The secondary outcome evaluated the impact of these meals on various blood markers, including blood glucose, LDL, HDL, total cholesterol (TC), TG, serum insulin, TSH, T4, and epinephrine.

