### 4.5. Assessment and Outcomes

#### 4.5.1. Indirect Calorimetry Procedure

Participants began by resting in a supine position for 15 minutes to allow their heart rate to stabilize. After this period, a calorimetry mask was placed on their faces, and they breathed normally for 20 minutes. During this time, the indirect calorimetry device measured oxygen consumption and carbon dioxide production, enabling the calculation of resting energy expenditure, food oxidation rates, and respiratory rate. It was essential that participants remained awake, alert, and still throughout the calorimetry period. 

The indirect calorimetry measurements were conducted in five stages: Once before the intervention in a fasting state, and then at 1-, 2-, 3-, and 4-hours post-intervention. Due to the high sensitivity of indirect calorimetry, strict conditions were maintained to ensure maximum measurement accuracy. 

Calorimetry was performed in a separate, quiet room, isolated from other participants and distinct from the sampling area. Movements within the room were minimized, and the temperature was controlled between 22 and 24 degrees Celsius. Participants were required to fast for 10 - 12 hours before the start of the calorimetry measurement, with their evening meal being consistent with their usual diet. They were also advised to avoid strenuous physical activity on the day of the visit, arrive at the study center by vehicle, and refrain from smoking. 

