#### 4.5.2. Appetite Evaluation

On the day of the study, participants completed a paper questionnaire at three key points: Before the intervention, one hour after the intervention, and at the conclusion of the intervention. This questionnaire assessed levels of satiety and hunger, with responses evaluated using a visual analog scale. To ensure consistency, participants’ attendance times were scheduled so that fasting did not exceed 12 hours. All measurements and evaluations were conducted between 7:00 am and 12:00 pm.

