#### 4.5.3. Blood Sampling Protocol

Blood samples were collected in three phases: At baseline (fasting state), one hour after the intervention, and four hours after the intervention. The primary objective was to compare blood parameters at one hour and four hours post-intervention with those measured at the fasting baseline. The parameters to be analyzed included blood glucose, LDL, HDL, cholesterol, TG, TSH, T4, and epinephrine.

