### 4.11. Expected Outcomes

#### 4.11.1. Primary Outcomes

The primary expected outcomes included the results of five indirect calorimetry measurements for each participant at each stage, as well as assessments of satiety conducted before the intervention, one hour after, and four hours after the intervention.

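### If the fasting reading is a level of time in the section 4.7 model, the meal main effect for RMR, RQ and satiety estimates only 0.80 or 0.67 of the post-meal difference

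*Protocol article*

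**What the plan says.** The opening of section 4 (Results) gives the primary aim: to "investigate and compare the postprandial acute effects of two different meals". Section 2 lists appetite response, RMR, diet-induced thermogenesis (DIT) and RQ under the primary objective.

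Section 4.5.1 times the calorimetry: "Once before the intervention in a fasting state, and then at 1-, 2-, 3-, and 4-hours post-intervention". Section 4.11.1 makes the whole series primary: "The primary expected outcomes included the results of five indirect calorimetry measurements for each participant at each stage". It adds satiety before the meal and at one and four hours.

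For appetite the article gives two schedules. Section 4.5.2 has three questionnaires: "Before the intervention, one hour after the intervention, and at the conclusion of the intervention". Section 3.1, in the text below Figure 1, has a fasting questionnaire and then says "IC and appetite response assessments were conducted four times at one-hour intervals" after the meal.

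The analysis sentence in section 4.7 is: "A two-factor repeated measures design was evaluated using generalized linear mixed models to examine the impact of time and type of meal across various phases". The same section describes record codes A to E, in which "the letters represented the fasting stage and subsequent hours post-intervention". Section 4.5.3 also uses the word phases for time points that include fasting: "Blood samples were collected in three phases: At baseline (fasting state), one hour after the intervention, and four hours after the intervention".

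**The concern.** The question is what happens after the meal. The fasting reading at a visit comes before that visit's meal. With an adequate washout, its expected difference between meals is therefore zero. In a two-factor model whose time factor includes fasting, the main effect of meal is the average of the meal difference over all time levels. It then mixes a known zero with the post-meal differences.

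Two things would be at stake. The reported meal effect would be smaller than the postprandial difference that readers would take it to be. The test would also lose power in a trial of 30 people.

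**Working it through.** **The plan's own figures.** Section 3.3 gives alpha 0.05, beta 0.2 and 30 participants. It gives no means, SDs or attrition rate, so 30 cannot be reproduced. Only alpha, 80% power and n = 30 are carried forward.

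**Is fasting a level of time?** Section 4.7 does not say which levels enter the model. Three places point to inclusion:
- Codes A to E in section 4.7 are the within-visit time labels, and A is fasting.
- Section 4.11.1 counts the fasting reading among the five primary calorimetry results.
- Section 4.5.3 calls fasting one of the phases.

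One place points elsewhere: section 4.1 uses phase for the two crossover periods. Inclusion is therefore a supported inference, and what follows is conditional on it.

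**Size of the dilution.** Take one fasting reading with meal difference 0 and k post-meal readings with constant difference d. The main effect estimates (0 + k·d)/(k + 1).
- k = 4 (calorimetry; appetite under section 3.1): 4d/5 = 0.80d.
- k = 2 (satiety under sections 4.5.2 and 4.11.1): 2d/3 = 0.67d.

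**Power.** Assumptions: 30 completers with both visits, two-sided alpha 0.05, normal approximation, within-person meal differences of unit variance at each time, and a common correlation r between those differences.
- Variance of the post-meal mean: Vp = (1 + (k−1)r)/k.
- Variance of the mean over all readings: Va = (1 + kr)/(k + 1).
- Set d = (1.960 + 0.842)·√(Vp/30), so that the post-meal mean has 80% power.
- Power of the main effect: Φ[2.802·(k/(k+1))·√(Vp/Va) − 1.960].

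Example, k = 4 and r = 0.5: Vp = 2.5/4 = 0.625 and Va = 3/5 = 0.600. Then 2.802 × 0.8 × √(0.625/0.600) = 2.288, and Φ(2.288 − 1.960) = 0.628.

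The same set-up gives two comparators. The post-meal mean adjusted for fasting has variance Vp − r². The post-meal mean minus fasting, which is a meal-by-time contrast estimating the full d, has variance Vp + 1 − 2r.

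| k | r | Main effect, fasting included | Post-meal mean | Post-meal minus fasting | Post-meal mean, fasting as covariate |
|---|---|---|---|---|---|
| 4 | 0 | 70.7% | 80% | 24.0% | 80.0% |
| 4 | 0.3 | 64.4% | 80% | 54.1% | 87.5% |
| 4 | 0.5 | 62.8% | 80% | 80.0% | 95.1% |
| 4 | 0.7 | 61.9% | 80% | 98.1% | 99.6% |
| 4 | 0.9 | 61.3% | 80% | >99% | >99% |
| 2 | 0 | 62.8% | 80% | 36.6% | 80.0% |
| 2 | 0.3 | 54.1% | 80% | 59.7% | 85.5% |
| 2 | 0.5 | 50.8% | 80% | 80.0% | 92.9% |
| 2 | 0.7 | 48.6% | 80% | 97.1% | 99.0% |
| 2 | 0.9 | 47.0% | 80% | >99% | >99% |

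The main effect with fasting included is below the post-meal mean in every row. The covariate form is never below any other column.

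**The case against.** Several objections have force and limit the point.

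- **Inclusion is not stated.** The A to E codes are record labels, not a model specification. Section 4.5.3 goes on to compare the one-hour and four-hour blood values with fasting, which treats fasting as a reference. This stands, and it is why the finding is conditional. Nothing in section 4.7 excludes fasting, however.
- **Nothing makes the main effect decisive.** With fasting as a level, a meal-by-time contrast recovers the full d. This stands: only the main effect is diluted.
- **Not every primary outcome is affected.** DIT in its usual meaning is a rise over fasting, so it has no zero-effect level to average in. This stands.
- **The power model may not match the comparison made.** Section 4.7 also lists independent t-tests and a first-period covariance analysis. The percentages describe 30 paired visits and not those analyses. The factors 0.80 and 0.67 do not depend on sample size.

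A reader might also infer that leaving the deciding test open inflates the error rate. Simulation of one outcome under the null gives about 9-10% if either main effect or interaction may be claimed. It gives 16-21% (five readings) or 13-14% (three) if hourly tests count too. The documents do not support this as a finding: section 4.7 lists no hourly tests, and an analysis plan that is not shown may name the deciding contrast.

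A reader might further infer that the fasting reading should simply be discarded. The table shows otherwise: as a covariate it adds power whenever r exceeds zero.

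**Conclusion.** The point holds in conditional form. If fasting is a level of time, as the article implies without saying so, the main effect of meal is not the postprandial difference. For RMR and RQ it estimates 0.80d. For satiety it estimates 0.67d under sections 4.5.2 and 4.11.1, or 0.80d under section 3.1, and those sections must be reconciled. Where the post-meal mean has 80% power, the main effect has about 61-71% (five readings) or 47-63% (three).

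The factors assume a constant post-meal difference and no carryover into the fasting reading. The power figures also assume 30 paired completers and r between 0 and 0.9, since the article gives no variances or correlations. It would go too far to say that the model is known to include fasting, or that every primary outcome is diluted.

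**What to change.** In section 4.7, for RMR, RQ and satiety, name as the deciding contrast the HP-HF-LC minus HP-LF-HC difference averaged over the post-meal readings. Remove that visit's fasting reading from the response and from the time factor, and enter it as a covariate. Report the meal-by-time interaction and the hourly differences as supportive. Reconcile the number of post-meal appetite assessments between section 3.1 and sections 4.5.2 and 4.11.1, so that the average is defined.

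The cost is a few sentences and one changed model statement, with no new data or participants. The drawback is that a purely transient difference, present only at one hour, would count as supportive evidence and not as the main result.
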